## Abstract

**Background:**

Adults aged 65 and older with severe mental illnesses are a growing segment of the Dutch population. Some of them have a range of serious problems and are also difficult to engage. While assertive community treatment is a common model for treating difficult to engage severe mental illnesses patients, no special form of it is available for the elderly. A special assertive community treatment team for the elderly is developed in Rotterdam, the Netherlands and tested for its effectiveness.

**Methods:**

We will use a randomized controlled trial design to compare the effects of assertive community treatment for the elderly with those of care as usual. Primary outcome measures will be the number of dropouts, the number of patients engaged in care and patient's psychiatric symptoms, somatic symptoms, and social functioning. Secondary outcome measures are the number of unmet needs, the subjective quality of life and patients' satisfaction. Other secondary outcomes include the number of crisis contacts, rates of voluntary and involuntary admission, and length of stay. Inclusion criteria are aged 65 plus, the presence of a mental disorder, a lack of motivation for treatment and at least four suspected problems with functioning (addiction, somatic problems, daily living activities, housing etc.). If patients meet the inclusion criteria, they will be randomly allocated to either assertive community treatment for the elderly or care as usual. Trained assessors will use mainly observational instruments at the following time points: at baseline, after 9 and 18 months.

**Discussion:**

This study will help establish whether assertive community treatment for the elderly produces better results than care as usual in elderly people with severe mental illnesses who are difficult to engage. When assertive community treatment for the elderly proves valuable in these respects, it can be tested and implemented more widely, and mechanisms for its effects investigated.

**Trial Registration:**

The Netherlands National Trial Register NTR1620

## Background

Adults aged 65 plus are a fast-growing segment of the Dutch population. This sharp rise is leading to an increase in the number of elderly people who live on their own and who have psychiatric disorders [1,2]. Just 8%-16% of elderly people with such disorders receive treatment from a healthcare provider [1,3,4]. This group of older psychiatric patients is not only difficult to engage, but often also has a range of serious problems in other aspects of their lives [2]. Some of them neglect themselves and their immediate surroundings, and thus live in extreme squalor [5,6]. Exact numbers of (self)-neglected elderly are not known [5,6]. But elderly in the community with depressive symptoms or cognitive impairment are at risk for development of self-neglect [7] and more than half of the elderly who are neglecting their environment has a psychiatric disorder such as dementia, paranoid disorder, addiction or depression [6]. It is unknown whether mental healthcare services to date are sufficient to help them, e.g. because these patients drop out of care due to the lack of motivation, [8,9], or whether active outreach care, such as assertive community treatment (ACT), is needed.

In adult mental healthcare, ACT is a much-examined, frequently used organizational model for treating difficult-to-engage patients with severe mental illness (SMI; 10, 11). Particularly in the United States, ACT has been proven to be effective in reducing admissions and making patients' housing status more stable. It improves patients' satisfaction and motivation for treatment [12,13]. A relatively high number of ACT patients also remain in care [14,15]. We think this last observation is very important, since drop out of care may lead to further deterioration.

European studies, however, have been less unanimous about the effects of ACT and showed no difference between ACT and care as usual (CAU) in terms of psychosocial functioning and hospital admission days [16-18]. Part of this discrepancy may be explained by improvements in the quality of CAU in Western Europe [19,20], but also by the fact that CAU contains some features of ACT [21].

Intervention studies for SMI elderly in the community are rare. Two studies showed that intensive community care given to depressive elderly people (sometimes with delusions) caused a fall in the number of admissions to a psychiatric unit, stabilization of psychiatric symptoms, and an improvement in quality of life [22,23] as compared to CAU. Another study showed that psychiatric symptoms and functioning improved when elderly people with psychiatric problems received outreach services rather than office-based ones [3]. We found no studies that focused on the effects of ACT for patients aged 65 and over.

### Research aim

Using a randomized controlled trial (RCT) design, we will compare the effects of ACT elderly (ACTE) with those of CAU for elderly patients with SMI who are difficult to engage in care.

### Hypotheses

Our first hypothesis is that ACTE will decrease the number of patients who drop out of care (number of patients who have no registered contact with the services over a period of 3 months and/or the number of patients discharged out of care). The other primary hypotheses include that ACTE will increase the number of patients engaged in care (patients who receive care within 3 months after admission to the team) and will improve patients' psychiatric, somatic and social symptoms. Secondary hypotheses include that ACTE reduce the number of unmet needs more than CAU does. We also expect an increase in patients' subjective quality of life and in patients' satisfaction with mental-health care. Finally we hypothesize that to a greater extent than CAU, ACTE will reduce the number of crisis contacts, reduce voluntary and involuntary admission rates and reduce length of stay in a psychiatric hospital.

### Research design

This RCT will use one intervention group consisting of patients who receive treatment according to ACTE, and one control group consisting of patients who receive treatment according to CAU. We will use a pre-randomized block design, with four patients per block, whereby patients are randomized *before *they consent to participate, the so-called Zelen's design [24]. The design and execution of this study were approved by the Dutch union of medical-ethic trial committees for mental health organizations

### Participants - setting

The study was carried out in the Netherlands by BavoEuropoort centre for mental healthcare in the greater Rotterdam area (1.3 million residents). BavoEuropoort has 1,300 staff, who are employed at 32 sites in eleven municipalities. It provides treatment and guidance to people in whom complex psychiatric disorders are combined with problems in several life domains. It has various outpatient clinics and clinical settings for voluntary or involuntary admission. There are six ACT teams for patients who are difficult to engage in treatment. One of these teams focuses on elderly patients. BavoEuropoort also provides mental healthcare services for elderly people (55+) in their third and fourth stages of life who have mental health complaints and/or cognitive disorders.

Participants are elderly outpatients (aged 65 years or older) with severe psychiatric problems, who are difficult to engage, and who are resident in the BavoEuropoort catchment areas.

### Procedure

BavoEuropoort has one ACT team for elderly people (intervention condition). In the control condition (CAU), participants were identified by three general community mental health teams working for elderly people living in the community. Two of these teams focused on patients with psychiatric disorders; the other focused mainly on patients with cognitive impairments. Community mental healthcare professionals from these teams will use a checklist to determine whether all new elderly service-users meet the inclusion criteria. The inclusion of patients started July 2008 and was closed on 1 August 2010.

Figure 1 shows the inclusion flowchart; inclusion criteria are:

1. age 65 year or older;

2. having a severe mental illness (patients with a severe psychiatric disorder, usually psychotic or bipolar disorder or severe depression, leading to a complex combination of psychiatric and social needs).

3. no motivation for treatment (actively or passively resisting treatment; the patient is very difficult to involve in any form of treatment, including treatment by the general practitioner).

4. and 4 problems of the following domains:

- addiction: taking alcohol and drugs taking not in a social context, occasional minimal loss of control of drinking or drugs use or adverse consequences or incapacitated due to alcohol or drug problems.

- somatic problems: all kind of somatic problems, including illness or disability from any cause that limits mobility, impairs sight or hearing, or otherwise interferes with personal functioning.

- daily living activities: the overall level of functioning in activities of daily living: e.g., problems with basic activities of self-care such as eating, washing, dressing, toilet; also complex skills such as budgeting, recreation and use of transport, etc.

- housing: the overall severity of problems regarding the quality of living conditions, accommodation and daily domestic routine, taking into account of the patient's preferences and degree of satisfaction with such circumstances. Are the basic necessities met?

- daytime activities: the overall level of problems regarding the quality of the daytime environment. Limited or no daytime activities. The patients problems are made worse by a lack of daytime activities.

- social relationships: problems associated with social relationships, as identified by the patient or apparent to carers or others. These included active or passive withdrawal from social relationships, a tendency to dominate, social relationships or non-supportive, destructive or self-damaging relationships.

- finances: problems associated with finance (such as debts), and problems with skills such as budgeting.

- police contacts: contact within police in the last year that were a product of the patients psychological situation. Examples: nuisance, public drunkenness or minor offence by psychological situation.

We exclude patients with severe cognitive problems (severely disorientated, for example consistently disorientated with regards to time to time, place, or person, or suffering memory impairment for example only fragments remain, loss of distant as well as recent information, unable to effectively learn any new information, no effective communication possible through language or inaccessible to speech.

Primary and secondary outcome variables were collected by means of an interview of patients willing to give informed consent as well as from the patients' files. A trained independent research assessor will record these primary and secondary outcome measures. This research assessor contacts after patient randomization the clinician to make an appointment to visit the patient together. In this contact with the patient the research assessor asked questions (via semi structured interview) to rate the assessment instruments. Because patients are difficult to engage they don't fill in questionnaires themselves. If patients refuse to answer questions, the research assessor will collect data from the patient's records or via asking the clinician about the patients' situation. Data are collected as part of the routine outcome assessments of the mental health centre. The first interview was done closely after inclusion in the study. The second interview took place 9 months after the first and the last interview after 18 months.

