#### QoL

Quality of life will be measured using the QoL scale, which has shown itself to be well suited to measuring satisfaction in the chronic psychiatric target group [33,34]. Dealing with patients' subjective perceptions with respect to quality of life, the scale consists of six elements covering patients' satisfaction with their 1.) life as a whole, 2.) living situation, 3.) personal relationships 4.) physical health, 5.) mental health and 6.) financial situation. Per item, the researcher will ask the patient to award a score on a 7-point Likert scale ranging from 1 (bad or not at all satisfied) to 7 (good and very satisfied).

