#### Satisfaction with the care-provider

The QoL scale will be extended with one question on patients' satisfaction with their treatment. This will be taken from the satisfaction questionnaire [34], and, like all answers in the QoL, be rated as a single question on a 7-point Likert scale.

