## Discussion

The central research question in this study is whether ACTE can ensure that elderly people with SMI remain in care and whether ACTE can reduce psychosocial symptoms and unmet needs more than CAU. Other research questions include whether the intervention can reduce the number of crisis contacts, reduce the number and duration of voluntary and involuntary admissions, and improve quality of life and client satisfaction.

This study will thus provide opportunities to examine how well ACTE works in practice with this group of elderly people, and whether it has any extra value over CAU. By helping to increase overall understanding of various forms of mental healthcare, its implementation may lead to an evidence-based intervention for this special group. If ACTE is shown to have added value, it can be implemented, and further research can follow.

The study results will be prepared for national and international publication and for presentation at national and international conferences. They may also lead to the publication of a handbook on ACT for the elderly.

This study has two specific strengths and two limitations. The first strength is that we will use and RCT design to test the effectiveness of ACT for the elderly. The second is its internal validity, which is protected by the structured protocol monitoring the ACT model, as well assessing the contents of the CAU by also applying the DACTS scale.

The first limitation is the fact that community mental healthcare professionals and the independent research assessor will not be blinded for which patients are included in this study. Because the only way in which independent research assessor can reach elderly people with SMI is through collaboration with the community mental healthcare professionals, it will not be possible to blind them both. The second limitation is that CAU exists of different kind of teams in different area, with different working methods. These working methods will be describe in the outcome of the DACTS but can negatively or positively affect the outcome results. In addition, the effects of ACTE will also depend on the CAU. When the quality of care of the CAU is high, there is less chance of demonstrating an effect of ACTE. This limitation is a problem in all studies comparing a new intervention with CAU [49]. Therefore, we will describe CAU thoroughly also using the DACTS, to demonstrate in what aspects ACTE and CAU differ.

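### The refusal fallback exempts no interview-based instrument: as written, the treating clinician may supply quality-of-life and satisfaction answers, and the rule is not reconciled with carry-forward

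*Protocol article*

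**What the plan says.** The Procedure section of the protocol article describes one data-collection route for primary and secondary outcomes together, by interview and from patient files: "A trained independent research assessor will record these primary and secondary outcome measures". The assessor visits the patient with the clinician and rates the instruments from a semi-structured interview, since "Because patients are difficult to engage they don't fill in questionnaires themselves". The rule for refusal follows: "If patients refuse to answer questions, the research assessor will collect data from the patient's records or via asking the clinician", with the sentence closing on the patient's situation as the subject of the enquiry. It names no instrument to which it does or does not apply.

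Two of the secondary outcomes are defined as the patient's own judgement. The QoL section describes its scale as "Dealing with patients' subjective perceptions with respect to quality of life" and says how it is scored: "Per item, the researcher will ask the patient to award a score on a 7-point Likert scale". Under Satisfaction with the care-provider, "The QoL scale will be extended with one question on patients' satisfaction with their treatment", rated in the same way.

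Statistical analysis names the interviewer as collector of both measures. It says that missing data at the second and third interviews are replaced by the last interview held. The Discussion gives as a limitation that "community mental healthcare professionals and the independent research assessor will not be blinded".

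**The concern.** Refusal is not a rare event in this trial. Lack of motivation for treatment, including active or passive resistance, is an inclusion criterion, and the fallback was evidently written because refusals were expected.

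For an observer-rated scale, asking the clinician is a reasonable substitute. For a patient's subjective quality of life it changes what is measured. For satisfaction with care, the informant becomes the provider being judged, who knows the arm.

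There is a second issue for HoNOS 65+ and CANE. The share of ratings based on clinician or record information may differ between arms, because the arms handle reluctant patients differently. A difference in rating source could then be mistaken for a difference in outcome. HoNOS 65+ carries the psychiatric, somatic and social outcomes that Hypotheses and the outcomes section call primary, although Statistical analysis lists psychosocial functioning as secondary.

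Third, two rules in the article could apply to the same refused follow-up interview, and they can yield different values for the same patient.

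**Working it through.** The plan gives no figure on this point, so there is none to reproduce. The check is mainly a comparison of sections.

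1. **Which outcomes can the fallback reach?** Assessment instruments takes engagement, dropout, crisis contacts, admissions and length of stay from electronic records. Table 2 takes dropout, crisis contacts and admission days from the registration system. These sources apply to every patient, so refusing an interview does not change them. The fallback can reach HoNOS 65+, CANE, QoL and the satisfaction item.
2. **Is any of these four exempted?** Procedure has no exception. QoL says the patient awards the score. Table 2 and Statistical analysis name the interviewer. None of them says that a refused item stays missing.
3. **Which rule governs a refused follow-up?** Procedure would fill it from records or the clinician. Statistical analysis would carry the last interview forward if the interview counts as missing. Nothing says whether it does. A carried-forward value could itself rest on proxy information from an earlier refusal.
4. **Can the source differ by arm?** Intervention and care as usual says ACTE staff keep investing in the relationship when care is refused. Table 1 says refusal of contact in CAU usually leads to discharge. A refuser in ACTE may therefore have a well-informed clinician, while one in CAU may have only an older record or a clinician no longer in touch. Different source mixes are plausible, but the article gives no rates.

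**Illustration (all inputs assumed).** Let p be the share of an arm answered by proxy and b the amount by which the proxy exceeds the patient's own score, with A for ACTE and C for CAU.

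Bias in the arm difference = pA × bA − pC × bC

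- Over-rating in ACTE only, low case: 0.20 × 0.5 = 0.10 points on the 7-point item. With an assumed SD of 1.5, 0.10 / 1.5 = 0.07 SD.
- Over-rating in ACTE only, high case: 0.40 × 1.5 = 0.60 points, or 0.60 / 1.5 = 0.40 SD.
- Equal over-rating of 1 point, proxy share 10% in ACTE and 30% in CAU: 0.10 × 1 − 0.30 × 1 = −0.20 points, in favour of CAU.

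The 20% equals the loss quoted in Power analysis from another ACT trial. That figure combines ineligible patients with refusals of interview consent, so it is not a proxy rate; it serves only as a starting value.

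For scale, take the 64 patients recruited (Discussion), assumed to split 32 per arm, with no true effect. The standard error of a mean difference is √(2/32) = 0.25 SD. If 40% of each arm is answered by proxy and ACTE proxies are 0.5 SD more favourable than CAU proxies, the bias is 0.40 × 0.5 = 0.20 SD and the two-sided false-positive rate at nominal 0.05 becomes 0.126. With 20% by proxy the bias is 0.10 SD and the rate 0.069. With 10% and 0.25 SD it is 0.025 SD and 0.051, which is negligible.

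**The case against.** The strongest reply is that the fallback was never meant for the patient-reported items. Its closing words refer to the patient's situation, which suits observable problems and needs. The Abstract calls the instruments mainly observational. The QoL section has the patient give the score. Table 2 names the care provider as assessor only for the working-relationship scale, and Statistical analysis expects some interview data to be missing. This reading is plausible and may be what was intended. It does not settle the matter, because the one rule on refusal has no exception and the more specific sections do not say what happens when the patient declines.

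A reader might infer more than the article supports, in four ways.

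- That clinicians can supply any primary or secondary outcome. They cannot: the service-use outcomes, including dropout, come from records for everyone.
- That clinicians score quality of life or satisfaction. The article never says so. The assessor records the rating, and the clinician would at most supply the information.
- That the results are biased towards ACTE. The illustration changes sign with its assumptions.
- That the article is deficient for having no analysis by rating source. A condensed article may leave that to the full protocol or analysis plan, which are not shown. The defect lies in the stated rule; the sensitivity analysis is part of the remedy.

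Lack of blinding is already disclosed, with a reason. The disclosure does not address who answers for a patient who refuses.

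**Conclusion.** The point holds as a defect in the stated procedure. As written, the refusal rule permits an unblinded treating clinician to be the source for two secondary outcomes defined as the patient's own score. It is also not reconciled with the carry-forward rule for missing follow-up interviews. For HoNOS 65+ and CANE proxy information is acceptable in principle; the remaining risk is a source mix that differs by arm.

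The size is undetermined. Proxy share, over-rating and SD are assumptions, and plausible values range from a negligible effect to several tenths of a point in either direction. The conclusion rests on the wording of the rules and does not depend on those figures. The dropout comparison is untouched. The change is worth making because it is cheap and refusal is to be expected in this population.

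**What to change.** 1. State that the record or clinician fallback applies only to HoNOS 65+ and CANE.
2. Treat refused QoL and satisfaction items as missing, not replaced by clinician or record information. If any such value has been obtained by proxy, set it to missing.
3. Report QoL and satisfaction response rates by arm and visit, and state that a comparison among responders is itself open to selection that depends on arm.
4. Say which rule, proxy or carry-forward, governs a refused follow-up interview for each instrument.
5. Record the source of each HoNOS 65+ and CANE rating (patient interview, clinician or record), and add one sensitivity analysis by source.

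The cost is a few sentences, one source field per assessment and one extra analysis. If sources were noted at the time, the last step remains possible after data collection. The downside is more missing QoL and satisfaction values, and so less precision on two secondary outcomes. The selection problem in step 3 is not removed, only made visible.
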